|  |  | ***Participant recruitment***  The person-in-charge of residential care facilities and the non-governmental organizations that serve adults with ID, including the Hong Chi Association who had collaborated with us in our pilot project, will be approached by the research team to seek their collaboration and support in recruiting participants and implementing the project. The research team will organize promotion talks and distribute promotion leaflets of the project to potential participants and their families or guardians. To ensure safety of the participants, PA pre-participation health screening will be performed in accordance with the guidelines of American College Sport Medicine (ACSM, Appendix 1). Medical clearance/approval to participate MVgPA will be sought if they have known cardiovascular, metabolic and/or renal disease, or signs and symptoms suggesting these diseases (as detailed in Appendix 1). An information sheet related to the MVgPA, including the heart rates during the PA and type of exercise, will be provided to the physicians. The eligibility of the participants will be screened based on the following criteria:  *Inclusion criteria:*   1. Chinese adults who are aged 18 years to 64 years and are diagnosed with mild or moderate ID based on the information provided by the residential care facilities; 2. Able to understand basic information and instructions of the intervention and to make decisions upon their participation; 3. Classified as physically inactive (i.e., <150-min moderate-intensity or 75-min vigorous-intensity PA/week, see Appendix 1); 4. Currently using residential service user as stated in the Social Welfare Department (https://www.swd.gov.hk/en/index/site_pubsvc/page_rehab/sub_listofserv/id_sermentalhandi/).   *Exclusion criteria:*   1. Currently enrolled in a regular exercise program; 2. Physically unable to participate in the MVgPA, such as having significant mobility problem; 3. Participation to MVgPA will put them at physiological risk; or 4. At risk of self-harm as determined by the staff of the residential care facilities.   ***Sample size calculation***  A similar study for adults with ID in community residences showed an effect size of 0.41 on PA level change^20^. Assuming a similar effect size on PA level change in our proposed trial, a sample size of 119 participants per each of the control and intervention groups will provide the study with 80% power at 2-sided 5% level of significance, as estimated using the power analysis software PASS 13.0 (NCSS, Kaysville, USA). Furthermore, to account for potential reduction in statistical efficiency due to randomization by residential care facilities (clusters) instead of individual participants, a variance inflation factor, called design effect, will be applied to impose to the estimated sample size. The design effect is given by 1 + (m–1)*ICC, where m=average cluster size and ICC=intracluster correlation coefficient of the underlying outcome. We anticipate that the outcomes of the participants recruited from the same residential care facility are unlikely correlated with one another, particularly for the PA outcome. In this regard, the ICC would be small. A synthesis study revealed that ICC tends to be small in primary care research with a median of 0.005 and inter-quartile range of 0.000 to 0.021^21^. Allowing for a conservative ICC of 0.01 and up to 20% attrition rate in our proposed study, at least 17 participants per each of the 14 residential care facility are therefore required.  ***Cluster randomization***  Randomization will be performed at the cluster level (residential care facility) instead of individual participants to avoid contamination between the intervention and control groups. Baseline data for all participants in each cluster will be completed before randomization. The facilities will be randomized to either intervention or control group in a 1:1 ratio. Eligible participants recruited from the same facility will be allocated to either intervention or control groups accordingly. Group allocation will be concealed from outcome assessors and made according to the random group allocation sequence generated by an independent statistician and the sequence of entry into the study. |

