|  | (vii) | Results analysis |
|  |  | Appropriate descriptive statistics will be used to summarize and present the study data. Skewed continuous variables will be appropriately transformed before analysis. By considering the potential design effect of the randomization conducted in cluster level instead of individual participants, the outcome analysis will be performed on the basis of a three-level mixed effects model accounting for inter-correlation among individuals within the same cluster as well as intra-correlation over time within an individual and variations between individuals. This type of model can account for intra-correlated clustered and repeated measures data and produce unbiased estimates even in the presence of missing data, provided that the data are missing at random. Mixed-effects model will be used to compare the differential changes in each outcome variables (PA level, PA self-efficacy and interest, and exercise capacity) across time (T0, T1, T2) between the two groups. Positive significant group-by-T1 and group-by-T2 interaction-terms in the mixed-effects models indicate significantly greater increment of intervention group in the underlying outcome than the control group at the respective time-points with respect to T0.  The primary analysis of the outcome comparisons will be conducted on the basis of intention-to-treat principle, That means all the randomized participants will be included in the analyses and analyzed according to the groups they are originally allocated. Since all the baseline data, including outcomes, will be collected from all participants before randomization, so all the participants should have at least one measurement (observation) for each outcome and can be included in the mixed-effects model for outcome comparison. For participants who could not follow the intervention owing to the change in medical conditions or other reasons, their data will be continued to be collected at the follow-up time points. If there are considerable missing follow-up data, say >10%, sensitivity analysis will also be conducted to assess the robustness of the primary analysis results. In this connection, multiple imputation method will be used to impute missing data, using all available baseline characteristics as covariates. Predictive mean matching approach^30^ which relies less on the parametric assumptions of the imputation models will be used. Furthermore, a post hoc subgroup analysis will be performed to examine the effects of the intervention between those with and those without Down syndrome if a considerable proportion of the participants have such syndrome. Cohen’s d effect sizes will be computed for the outcomes to demonstrate the effectiveness of the programme. All statistical analyses will be conducted using SAS release 9.4 (SAS Institute Inc, Cary, NC). All statistical tests involved will be two-sided with level of significance set at 0.05. |

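### The primary contrast, read as a difference in change from T0, does not use the equality of baseline means that pre-randomization measurement guarantees; stating that constraint would raise precision at no extra cost in data

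*Protocol*

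**What the plan says.** The Results analysis section specifies a three-level mixed model (facility, participant, time). It states that "Mixed-effects model will be used to compare the differential changes in each outcome variables" across T0, T1 and T2. Positive, significant group-by-T1 and group-by-T2 interactions are to be read as a larger increment in the intervention arm relative to T0. The T0 value is part of the response: the section relies on every participant having at least one observation so that all can enter the model. It mentions neither a baseline covariate nor a common baseline mean, and it does not say whether a group main effect is included.

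The Cluster randomization paragraph says that "Baseline data for all participants in each cluster will be completed before randomization", and the Results analysis section repeats this for the outcomes.

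The Sample size calculation assumes "an effect size of 0.41 on PA level change" and states that "a sample size of 119 participants per each of the control and intervention groups" gives "80% power at 2-sided 5% level of significance". For clustering, "The design effect is given by 1 + (m–1)*ICC". The final target, "Allowing for a conservative ICC of 0.01 and up to 20% attrition rate in our proposed study", is at least 17 participants in each of 14 facilities.

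**The concern.** With group, time and group-by-time terms in the model, the interaction at T1 or T2 is the arm difference at that visit minus the arm difference at T0. The T0 difference is estimated from the data and subtracted in full. Because baseline is measured before allocation, the true T0 difference is zero, and what is observed is chance. Subtracting all of it adds noise. Unless baseline and follow-up are perfectly correlated, it also over-corrects for whatever imbalance happens to occur.

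Precision on the primary outcome is what is at stake. The trial randomizes only 14 facilities, and its recruitment target leaves no room for the design effect it says it will apply. A gain in precision from data already being collected is worth having.

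**Working it through.** **Inputs from the protocol (Sample size calculation).** Effect size 0.41, two-sided 5%, 80% power, 119 per arm, ICC 0.01 (the cited synthesis gives a "median of 0.005 and inter-quartile range of 0.000 to 0.021"), attrition 20%, 14 facilities of 17 allocated 1:1.

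**Assumed, because the protocol does not give it.** R, the baseline to follow-up correlation of the arm means, varied from 0.5 to 0.9. The 0.41 is taken in units of the SD of change, and facility effects are taken to vary over time, so that the full design effect applies to the change contrast.

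**Step 1: reproduce the stated size.** A two-sample t-test at 0.41 with 80% power needs 95 per arm. 95/0.8 = 118.75, so 119. The stated figure is therefore already inflated for attrition. The final target is 14 × 17 = 238 = 2 × 119, so no design effect has been applied.

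**Step 2: power of the planned contrast.**
- Completers per arm: 119 × 0.8 = 95.2; per facility: 95.2/7 = 13.6.
- Without clustering: Φ(0.41 × √(95.2/2) − 1.96) = Φ(0.869) = 80.8%.
- Design effect at ICC 0.01: 1 + 12.6 × 0.01 = 1.126. Effective n: 95.2/1.126 = 84.5.
- With clustering: Φ(0.41 × √(84.5/2) − 1.96) = Φ(2.666 − 1.96) = 76.0%.

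**Step 3: variance with a common T0 mean.** Let V be the variance of the arm difference at one visit.
- Difference in change: 2V(1 − R).
- Baseline means constrained equal: V(1 − R²).
- Ratio: (1 − R²)/[2(1 − R)] = (1 + R)/2.

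The ratio never exceeds 1, so in large samples the constraint costs no efficiency.

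**Step 4: power with the constraint.** The 2.666 is divided by √((1+R)/2). Normal approximation:

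| R (assumed) | Variance reduction | Power, ICC 0.01 | Power, ICC 0.021 |
|---|---|---|---|
| No constraint | – | 76.0% | 71.1% |
| 0.5 | 25% | 86.8% | 82.8% |
| 0.7 | 15% | 82.4% | 77.9% |
| 0.9 | 5% | 78.1% | 73.3% |

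For ICC 0.021, the upper quartile cited, the design effect is 1 + 12.6 × 0.021 = 1.265.

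**Step 5: when is the clustering loss fully recovered?** When (1+R)/2 × DE ≤ 1, that is R ≤ 2/DE − 1. This gives R ≤ 0.78 at ICC 0.01 and R ≤ 0.58 at ICC 0.021. At an assumed ICC of 0.05 (DE 1.63) it gives only R ≤ 0.23.

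**Step 6: small number of clusters.** With a t reference on 14 − 2 = 12 degrees of freedom and ICC 0.01, the planned contrast has 68.7% power. The constrained model has 80.6% at R 0.5 and 75.6% at R 0.7.

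**The case against.** **The constraint may already be intended.** A constrained model is also reported through group-by-T1 and group-by-T2 terms, and the protocol never says that a group main effect is fitted. That is right: free baseline means are inferred. But the stated contrast is a difference in change relative to T0 with no baseline adjustment, and a programmer following the text would most likely fit the ordinary group-by-time model. The point concerns the contrast the protocol does state, not a detail it leaves out.

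**The planned analysis is standard and valid.** This stands. A reader might infer that chance imbalance biases the estimate. Over repeated randomizations it does not; the over-correction is conditional on the imbalance observed. At ICC 0.01 the SD of the baseline difference between arms is about √(2 × 1.16/119) = 0.14 SD, so large imbalance is not a foregone conclusion.

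**The starting power is uncertain.** This also stands. The protocol does not say whether 0.41 is in SD-of-change or SD-of-level units. If facility effects are stable over time, they cancel from a T0-referenced contrast: with 0.41 in level units, a participant-level correlation of 0.5 and ICC 0.01, the planned contrast has 81.1% power and clustering costs nothing. If 0.41 is in level units and R is about 0.7, it already has about 91% or more. The factor (1+R)/2 does not depend on the SD scale; only the power figures do.

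**Twenty per facility.** The delivery section speaks of twenty participants in each intervention facility, against at least 17 in the sample size section. The two need reconciling, and the power figures would shift with the answer.

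**Conclusion.** The planned contrast, on its natural reading, is valid but inefficient. Because baseline precedes randomization, a common T0 mean is justified by design and reduces the variance of each treatment contrast by (1 − R)/2: 25%, 15% or 5% at R of 0.5, 0.7 or 0.9. On the assumptions in the working (0.41 in SD-of-change units, 95.2 completers per arm, ICC 0.01, facility effects varying over time, normal approximation), power moves from 76.0% to 86.8%, 82.4% or 78.1%.

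A reader might infer that this change makes good the power lost to clustering. The documents do not support that as a general statement. They give no R, and recovery is only partial at R 0.9, at ICC 0.021 with R 0.7 (77.9%), or with a 12-df t reference at R 0.7 (75.6%). The missing design effect remains a separate error in the sample size.

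A reader might also treat adjustment for T0 as a covariate as the same remedy. It is not: modelling only T1 and T2 given T0 drops participants who have a baseline value alone, whereas the protocol's intention-to-treat text counts on their being included.

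**What to change.** In the Results analysis section, state that the three-level model takes T0, T1 and T2 as outcomes, constrains the T0 mean to be equal across arms (no group main effect at T0), and uses group-by-T1 and group-by-T2 as the treatment effects. This keeps every randomized participant, including those with baseline only. Fix the wording before outcome data are unblinded.

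The cost is one sentence of model specification, with no extra participants, visits or measurements.

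Separately, correct the sample size for the design effect the protocol says it will apply. State the SD scale of the 0.41, and show power over a range of R and ICC instead of relying on the constraint to close the gap.

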|  |  | The reach-effectiveness-adoption-implementation-maintenance (RE-AIM) framework will be used to evaluate the acceptability and effectiveness of the intervention.  ***Reach*** will be measured by the proportion of eligible adults with ID who have received and completed the intervention relative to the number of adults with ID who have been approached to participate in the program, which will be recorded during the project.  ***Effectiveness*** will be measured by determining whether the following are observed among participants in the intervention group, compared to those in the control, after the intervention:   - a greater increment of at least 0.35 standardized mean difference (SMD) in mean PA level as measured by their time spent in moderate-to-vigorous PA on the basis of empirical evidence^22^; - a greater increment of at least 0.5 SMD in mean level of PA self-efficacy and interest; and - a greater increment of at least 0.5 SMD in mean functional exercise capacity as measured by conducting a 6MWT.   A 0.5 SMD is equivalent to a medium effect size and is conventionally accepted as clinically relevant difference. The satisfaction level of the participants and the staff will also be determined to assess the acceptability of the intervention.  ***Adoption*** will be measured by the proportion of potential residential care facilities that agreed to promote and implement our intervention relative to all facilities that have been approached, which will be recorded during the project.  ***Implementation*** will be measured by the number of intervention sessions that have been delivered at the residential care facility and the number of participants in each session. Attendance will be taken at each intervention session held at each residential care facility.  ***Maintenance*** will be measured by the proportion of residential care facilities allocated to intervention group that have expressed their willingness to continue implementing the intervention at their centres at post-intervention and the number of MVgPA sessions conducted in a 3-month follow-up period. |
|  | (vi) | Evaluation plan |

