|  |  | This project will adopt a cluster-randomized controlled group design to examine the effectiveness of the MVgPA.  **Data collection procedures**  Written consent will be obtained from the participants and their parent or guardian before the data collection. The PA level, PA self-efficacy and interest, and functional exercise capacity of the participants will be measured at the baseline (T0), one week post-intervention (T1) and three months post-intervention (T2) by a trained research assistant (RA2) who is blinded to the group allocation. Information on the sociodemographic and clinical characteristics of the participants will be collected by means of a demographic data sheet via interview and reviewing their record. In addition, the PA organized by the residential care facilities during the study period will also be recorded.  **Outcome measurement**  The PA level of participants (primary outcome) will be assessed in terms of minutes of moderate-to-vigorous PA by using an activity tracker (Fitbit Charge 2), which has demonstrated validity as compared with a research-grade accelerometer, and has been used extensively in western and local studies of adults with ID^9,27,28^. The PA level will be calculated as the average time (minutes) of moderate-to-vigorous PA after five consecutive weekdays of measurement at T0, T1 and T2, as they might go back home during the weekend. The staff of residential care facilities will be asked to remind participants to wear the activity tracker during all waking hours except in wet environment, such as showering, and continue with their usual daily activities during the measurement. The staff of residential care facilities will also be asked to help participants to record the time and reason that the activity tracker is put on and taken off each day.  PA self-efficacy will be measured by using the Chinese version of the self-efficacy scale of the baseline interview questionnaire (BIQ-C)^15^, which includes five items pertaining to the confidence of an individual in performing exercise. The items are rated on a three-point Likert scale (1=not at all sure; 3 = totally sure). The BIQ-C has demonstrated acceptable reliability (Cronbach’s ɑ = 0.75) and construct validity among the Chinese adults with ID^15^.  The functional exercise capacity of the participants will be assessed by conducting 6MWT, which has shown to be reliable and valid when used on adults with ID^29^. The participants will be asked to walk as quickly as possible on a flat, hard surface along a straight path in a period of 6 min.  The interest in performing PA and satisfaction level of MVgPA program of participants will be assessed by using a visual analogue scale (VAS), which consists of a 100 mm long line with the left anchor representing “no interest/not satisfied at all” and the right anchor representing “most interested/most satisfied”.  The satisfaction of residential service providers with the MVgPA intervention and their willingness to continue with the program will be measured at T1 by using an author-developed questionnaire. The staff involved in the MVgPA will be asked to rate their satisfaction and willingness on a six-point Likert scale.  **Ethical considerations**  Ethical approval will be sought from the research ethics committee of the study institution. Participants and their parents/guardians will be assured of confidentiality of any data collected, their participation is voluntary and of their right to withdraw from the study at any time without giving a reason, which will not affect their treatment or relationship with their service providers and the university. |

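### The single primary outcome is tested at T1 and at T2, each at two-sided 5%, and no primary time point is named

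*Protocol*

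**What the plan says.** Section (vi), Evaluation plan, names one primary outcome: "The PA level of participants (primary outcome) will be assessed in terms of minutes of moderate-to-vigorous PA". It is measured at T0, T1 and T2, and none of these is singled out.

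Section (vii), Results analysis, gives the reading rule for the mixed model: "Positive significant group-by-T1 and group-by-T2 interaction-terms in the mixed-effects models indicate significantly greater increment of intervention group" in the outcome concerned "than the control group at the respective time-points with respect to T0". The same section adds: "All statistical tests involved will be two-sided with level of significance set at 0.05".

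The sample size calculation in section (i) rests on a similar study that "showed an effect size of 0.41 on PA level change" and states that 119 per group "will provide the study with 80% power at 2-sided 5% level of significance". It names no time point.

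Section (v), Indicators and targets, lists under the Effectiveness item of RE-AIM "a greater increment of at least 0.35 standardized mean difference (SMD) in mean PA level". It places this after the intervention without choosing between T1 and T2.

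**The concern.** A single primary outcome normally gives a trial one test and one error rate. Here the outcome yields two group-by-time contrasts, each at the full 5% and each supporting its own conclusion, with no order between them. A reader of the results could take either one as the primary finding. The trial then has two chances at its main claim, and the choice of time point could be made after the results are seen.

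The power statement is affected too. The 80% belongs to one comparison at 5%, and the protocol does not say which. If success means either contrast, the error rate is above nominal. If it means both, the power is below 80%.

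**Working it through.** **Inputs from the protocol.** Two contrasts (T1 against T0, T2 against T0), each at two-sided 0.05; effect size 0.41; 80% power; 119 per group; 20% attrition; 14 facilities of 17; ICC 0.01. **Assumed.** The correlation r between the two test statistics, which the protocol does not give. If the three measurements have equal variance and equal pairwise correlation ρ, the contrasts share T0 and r = σ²(1−ρ) / [2σ²(1−ρ)] = 0.5. Other patterns give other values, so a range is shown.

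**Step 1: the protocol's own figure.** For one two-group comparison, n = 2(1.96 + 0.84)²/0.41², which gives 94 per group, or 95 with the t distribution. Dividing by 0.8 for attrition gives 95/0.8 = 118.75, so 119. The stated number is thus that of one test at 5%. No second test enters it.

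**Step 2: error rate if either time point suffices.** With independent tests, 1 − 0.95² = 9.75%. Counting only positive results, 1 − 0.975² = 4.9%. With correlated tests, the bivariate normal probability 1 − P(|Z1| < 1.96, |Z2| < 1.96), and its one-directional counterpart, give:

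| r | At least one false positive (nominal 5%) | At least one in favour of the intervention (nominal 2.5%) |
| --- | --- | --- |
| 0 | 9.75% | 4.9% |
| 0.3 | 9.5% | 4.8% |
| 0.5 | 9.1% | 4.5% |
| 0.7 | 8.3% | 4.2% |
| 0.9 | 7.0% | 3.5% |

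**Step 3: power under each reading.** Take each contrast to have exactly 80% power, as the protocol states for one comparison:

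| r | Both significant | At least one significant |
| --- | --- | --- |
| 0.3 | 67% | 93% |
| 0.5 | 69% | 91% |
| 0.7 | 71% | 89% |
| 0.9 | 75% | 85% |

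The stated 80% matches neither column. It holds only if one time point is the primary one.

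**Step 4: the 0.35 figure.** With 17 × 0.8 = 13.6 analysed per facility and 7 facilities per arm, 95.2 remain per arm. The design effect is 1 + 12.6 × 0.01 = 1.126, so the effective number is 95.2/1.126 = 84.5 and the standard error of the SMD is √(2/84.5) = 0.154. Significance needs an observed SMD of 1.96 × 0.154 = 0.30 with a normal reference, or 2.18 × 0.154 = 0.335 with t on 12 degrees of freedom (14 facilities less 2).

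**The case against.** The strongest defence is that the two contrasts answer different questions, immediate effect and maintenance, and that each is reported for its own time point. On that view no joint claim is made and no inflation arises. A multiplicity procedure is also commonly left to a statistical analysis plan, which may exist here. And the word joining the two terms could mean that both are required, which would cause no inflation.

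Part of this stands. The inflation is conditional: it applies only if a positive result at either time point counts as success. The protocol also treats only positive terms as benefit. A reader might infer that a false claim of benefit has a chance of about 9%, but for that claim the relevant range is 3.5% to 4.9% against 2.5%. The defence does not remove the gap, though. The protocol itself writes the reading rule and the blanket 0.05, it calls PA level primary, and it states a power that fits one unspecified contrast. That more than one reading is open is the defect.

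A reader might also infer that section (v) sets a second pass-or-fail rule, an observed SMD of at least 0.35, that competes with the tests and that the trial was not sized for. The protocol does not support this. The figure is a RE-AIM programme target, listed beside reach, adoption, implementation and maintenance, and section (vii) never makes success depend on it. A target below the planning effect of 0.41 is not an error. The zone in which a result would be significant yet miss the target is also fragile: 0.30 to 0.35 with a normal reference, but only 0.335 to 0.35 with the t reference in step 4.

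**Conclusion.** The point holds in this form: one primary outcome, two unranked contrasts at 5% each, and no primary time point in the outcome, analysis or sample size text.

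Its size depends on the reading. Under the either reading, the error rate is roughly 1.4 to just under 2 times nominal (7.0/5 to 9.75/5, with similar ratios in the favourable direction). Under the both reading, joint power falls 5 to 13 percentage points short of 80%. These figures assume jointly normal test statistics, correlations that the protocol does not supply, and 80% power for each contrast as stated. They do not depend on the ICC or the cluster size.

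This is an ambiguity that should be settled before results are seen. It does not make the planned model invalid. The 0.35 target merits a clarifying sentence only.

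**What to change.** - **Section (vii):** name the group-by-T1 contrast on PA level as the single primary test at two-sided 5%. Test group-by-T2 on PA level at two-sided 5% only if T1 is significant. This fixed order controls the error rate over the two contrasts without splitting alpha.
- **Section (i), sample size:** state that the 0.41 effect and the 80% power refer to the change from T0 to T1.
- **Section (v), side note:** state that the 0.35 SMD is a programme benchmark, reported with its 95% confidence interval, and not a condition of the primary test. Say which time point it refers to.

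The cost is wording only, with no added participants or visits. The downside is that an effect seen only at T2 becomes supportive. Choosing T1 is a judgement: section (v) does not settle it, because T1 and T2 both follow the intervention. If the sponsor prefers that either time point can carry the claim, a Bonferroni split at 0.025 each would need 115 analysed per arm instead of 95, for 80% power at each time point.

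### The multiple-imputation sensitivity analysis names baseline characteristics but not arm; followed literally, it shrinks the treatment effect by about the missing fraction

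*Protocol*

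**What the plan says.** Section (vii), Results analysis, of the protocol makes a "three-level mixed effects model accounting for inter-correlation among individuals within the same cluster" the primary analysis and says that it will "produce unbiased estimates even in the presence of missing data, provided that the data are missing at random". The treatment effect is read from "Positive significant group-by-T1 and group-by-T2 interaction-terms in the mixed-effects models".

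The same section then adds a conditional check: "If there are considerable missing follow-up data, say >10%, sensitivity analysis will also be conducted to assess the robustness of the primary analysis results". The method is multiple imputation by predictive mean matching, and the covariates are stated: "multiple imputation method will be used to impute missing data, using all available baseline characteristics as covariates". Arm, facility and the outcomes observed at T1 or T2 are not mentioned, and no analysis that departs from missing at random is described.

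Three other places bear on the point. Under Cluster randomization in section (i), baseline data for a cluster are completed before it is randomised; section (vii) repeats this. Under Sample size calculation in section (i), the planned effect is 0.41 and attrition of up to 20% is allowed for. Section (v), Indicators and targets, sets the effectiveness target for physical activity at 0.35 standardised mean difference.

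**The concern.** An imputation model needs to contain the variables of the analysis model, above all the one whose effect is being estimated. The analysis here rests on the interactions of group with time. If arm is left out of the imputation model, predictive mean matching draws donors from both arms together, so two participants with the same baseline profile get imputed values from the same pool whichever arm they are in. The imputed part of the data then shows no difference between arms, and the estimate is a mixture of the real effect and zero.

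What is at stake is how the sensitivity analysis is read. It is offered to show whether the primary result is robust. If the imputation itself pulls the estimate down, a sound primary result could look fragile. The sentence fixes a covariate set, so an analyst who follows it faithfully would build the poorer model.

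**Working it through.** The protocol gives no figure for the imputation, so there is none to reproduce. The check takes the protocol's effect size and attrition as inputs.

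**Inputs from the protocol**
- Planned effect: δ = 0.41 (section (i), Sample size calculation).
- Missing fraction f: 10% is the trigger (section (vii)); 20% is the upper attrition allowance (section (i)).
- Allocation 1:1 by facility; 14 facilities of 17; ICC 0.01 (section (i)).
- Effectiveness target: 0.35 (section (v)).

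**Assumptions not in the protocol**
- Outcomes are missing completely at random, with the same f in both arms.
- For the simulation only: a correlation of 0.5 between time points, and the same effect at T1 and T2.

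**Closed form.** Let the control mean at follow-up be μ and the intervention mean μ + δ. With arm left out and baseline balanced by randomisation, imputed values in either arm have expected mean μ + δ/2, the pooled mean of the observed values.
- Intervention mean after imputation: (1 − f)(μ + δ) + f(μ + δ/2)
- Control mean after imputation: (1 − f)μ + f(μ + δ/2)
- Difference: (1 − f)δ

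The result does not depend on the correlation between time points.
- f = 10%: 0.41 × 0.90 = 0.369
- f = 20%: 0.41 × 0.80 = 0.328
- f = 30% (beyond the allowance, to show the trend): 0.41 × 0.70 = 0.287
- The estimate reaches 0.35 at f = 1 − 0.35/0.41 = 0.146, or about 15%. That lies between the trigger and the allowance.

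**Simulation of predictive mean matching.** Settings: 14 facilities of 17, ICC 0.01, true effect 0.41, T2 values missing completely at random, 5 donors, 5 imputations, 600 runs. The estimate is the difference between arms in mean change from T0 to T2. Monte Carlo standard error is about 0.005 to 0.006.

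| Imputation model | 10% missing | 20% missing | 30% missing |
| --- | --- | --- | --- |
| Baseline only | 0.37 | 0.33 | 0.28 |
| Baseline + T1, no arm | 0.39 | 0.36 | 0.33 |
| Baseline + arm | 0.42 | 0.40 | 0.41 |
| Baseline + arm + T1 | 0.40 | 0.41 | 0.41 |
| Baseline + facility indicators | 0.41 | 0.41 | 0.40 |

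A separate simulation without clustering (119 per arm, 20% missing, correlation 0.5, 10 imputations, 400 runs) gave 0.32 without arm and 0.40 with it.

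**What the table separates.** The baseline-only row follows the closed form. Adding arm removes the shrinkage, whether or not T1 or facility is also in the model. Facility indicators remove it too, because arm is nested in facility. T1 without arm removes only part of it. So the shrinkage comes from leaving out arm, or facility as its carrier.

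**The case against.** The strongest reply is that the sentence excludes nothing. It says that baseline characteristics will be used. It does not say that they alone will be used, that arms are pooled, or that T1 is ignored. Facility is known before randomisation and can fairly be counted as a baseline characteristic; on that reading facility indicators carry arm and the shrinkage disappears. Imputation by arm could also be set in an analysis plan that is not at hand. All this stands, and it is why the point is conditional on a literal implementation. It does not remove the point: the covariate set is the one part of the imputation model that the protocol states, and arm is not in it.

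Several stronger readings are tempting and are not supported:
- *Leaving out facility and T1 also shrinks the effect.* With arm in the model and both of these left out, the estimates were 0.42, 0.40 and 0.41. Leaving out T1 discards information and weakens the missing-at-random assumption. Leaving out facility when arm is included is a matter of clustering variance.
- *The imputation simply uses less information than the mixed model.* The mixed model as described lists no baseline covariates, and the imputation adds them. Read literally, the imputation has more baseline and less follow-up information.
- *Any disagreement with the primary result would be an artefact.* It could be. It could also reflect missingness that depends on baseline factors, or weaker distributional assumptions, which is the protocol's stated reason for predictive mean matching ("which relies less on the parametric assumptions of the imputation models will be used").
- *The check will be run at 20% missing.* That figure is an upper allowance, and section (vii) keeps collecting data from participants who cannot follow the intervention. At the trigger the shrinkage is about 10%.
- *The protocol promises a test of departures from missing at random and fails to give one.* It promises a robustness check in general terms. Both analyses assume missing at random, so agreement between them would not speak to departures from it, but the document does not claim otherwise.

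**Conclusion.** The point holds in conditional form. Followed literally, the stated imputation model leaves out arm and reduces the effect in the imputed data by about the missing fraction: 0.41 becomes about 0.37 at 10% missing and 0.33 at 20%, and falls below 0.35 from about 15%. This rests on data missing completely at random, equal missingness in the two arms, facility not being entered as a covariate, and 0.41 and 0.35 being on the same standard-deviation scale. If T1 is used without arm, the loss is smaller (0.39 and 0.36 under the simulation's assumptions).

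A reader might infer that the trial's main result is biased. It is not: the imputation is a conditional sensitivity analysis, and the primary three-level model contains arm and is unaffected. Under these assumptions the error is towards no effect, so the risk is that a correct primary result is wrongly doubted.

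**What to change.** Amend the imputation sentence in section (vii) to say that imputation is done separately by arm, or with arm in the model; that the outcome at T0, T1 and T2 is included alongside the baseline characteristics; that facility is accounted for; and that the imputed data are analysed with the same three-level model. Predictive mean matching can stay.

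If robustness to the missing-at-random assumption is to be claimed, add a delta-adjusted (tipping-point) analysis on the same imputations: shift the imputed intervention-arm values by a range of amounts and report where the conclusion changes.

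The cost is a reworded sentence and a little more analysis work. No new data are needed and the primary analysis does not change.
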